### Sample size

2.3

There are no previous clinical trials to explore the beneficial effect of *TCPSQ* on college students from the integrating with physical fitness and psychological well-being. Therefore, this study is designed as a pilot study to calculate the appropriate sample size for future randomized clinical trials. Each group should include 30 participants, which is the minimum sample size for evaluating the effect of *TCPSQ*. Considering a 20% attrition rate, a total of 80 participants are necessary, with 40 participants in each group.

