### Participant and recruitment

2.4

A total of 80 college students from BUCM who are in the first or second grade aged 18 to 25 years will be recruited into the study. Recruitment plan of participants will be performed at the campus of BUCM by schoolyard media advertisement, posting up posters, and school radio, sending leaflets and brochures. Those who are interested in taking part will contact the research assistants directly who will determine eligibility according to the inclusion and exclusion criteria at the recruitment office. The research assistants will briefly explain the purpose of the study and ask if they have an interest in participating. If an applicant meets the study criteria, he or she will be required to sign a written informed consent agreement before enrollment in this trial. Participants will also be asked to sign a declaration stating that they will participate fully to the best of their ability and will continue their involvement in the *TCPSQ* program once commenced. A log book will be given to each participant to monitor involvement and practice *TCPSQ* as well as any reporting of adverse events (AEs).

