#### Intervention regimen

2.11.3

*TCPSQ* training consisted of an initial workshop conducted over 3 consecutive half-days by 2 qualified coaches. Participants received concentrated training: this consisted of instruction in source of *PSQ*, understanding in the essence and beneficial effects of *PSQ*. Participants will be taught the relevant knowledge of *TCPSQ*, which includes the rationale that *TCPSQ* constitutes a health benefit, the action essence of *TCPSQ* the philosophy opinion of *TCPSQ*. The instruction of *TCPSQ* will be both verbal and visual. And participants will be also obtained information about procedure of this study, and the matter needing attention of individuals in the trial. Participants will be required to learn the key movements known as “regulating body, breathe, mind” and ancillary exercises with multiple repetitions of *TCPSQ* until they master it, as will be confirmed by the professional coaches. The coaches will visit each individual daily to ensure that the movements are being correctly practiced.

Once initial concentrated training was complete, participants were asked to practice supervised training. Participants of *TCPSQ* group will undergo the regular training together for the last 10 weeks at a frequency of 5 days per week (from Monday to Friday), training will be performed for 50 minutes per day, each session will include a warm-up for 10 minutes. Specified *TCPSQ* performed and refined for 30 minutes, the practice method successively as follows: body adjustment; breathing adjustment; mind adjustment, and cooling down for 10 minutes. The instructors will visit each individual to ensure that the movements are being correctly practiced. All participants will be required to fill self-made *TCPSQ* training self-evaluation scale (including self-evaluation of training difficulty, the relaxation or tensity or pain and fatigue of various parts of body, perspiration level, saliva secretion level, body sense of warmth, breathing control state, meditative state of mind, abnormal physical and mental reaction, level of coordination between body and mind during and after training) and record their daily PA information during the intervention period. The compliance of the subjects will be assessed in terms of the number of training attended and the number of training self-evaluation scale per day.

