#### Secondary outcomes

2.13.4

Cardiopulmonary function, personality, self-esteem, quality of sleep, constitution in Chinese medicine, symptoms induced by spinal problems, and self-evaluation of Qigong training were regarded as secondary outcomes.

1.Cardiopulmonary function will be evaluated indirectly by blood pressure (BP), heart rate (HR). Also BP and HR will be tested by *HEM-746C electric sphygmomanometers* produced by the Omron Corp., China.2.Personality will be measured using EPQ-RSC revised by Gong Yaoxian and Chen Zhonggeng, etc. It consists of a 48-item self-report scale with 4 subscales: an extraversion/introversion scale (lower scores indicate more introversion), a neuroticism/stability scale (higher scores indicate greater emotional instability), a psychoticism/socialization scale (higher scores indicate being more reclusive, indifferent to others, and intransigent), and a lie scale. Only the first 3 personality traits were included in our analysis. The lie scale was used to assess the acceptability of respondents’ answers. Participants provided a yes or no response, and responses are scored 1or 0, respectively, except for some reverse-scored items. These 4 traits have been shown to have good factorial similarity across 34 countries in a study that analyzed gender-specific data. In the current sample, Cronbach's coefficient for the EPQ-RSC ranged from 0.62 to 0.72.^[93,94]^3.RSES will be adopted to measure self-esteem. We will use the Chinese version of RSES translated by Ji and Yu.^[95]^ It consists of 10 items, and the total score ranges from 10 to 40. Higher scores indicate higher self-esteem.4.Quality of sleep will be indexed by PSQI.^[96]^ The locally validated Chinese version of the PSQI is a self-report questionnaire that assesses multiple dimensions of sleep over the past month. Nineteen individual items generate 7 component scores: subjective sleep quality, sleep latency, sleep duration, habitual sleep efficiency, sleep disturbances, use of sleeping medication, and daytime dysfunction. The sum of the 7 component scores ranges from 0 to 21; The sum of the 7 component scores yields one global score of subjective sleep quality, higher scores represent poorer subjective sleep quality.5.Traditional Chinese Medicine body constitution will be evaluated with CCMQ. CCMQ is a self-rating scale with good reliability and validity that consists of 60 items scored on a 5-point scale, ranging from 1 (not at all) to 5 (very much). It has 9 subscales which assess one type of TCM constitution individually, including neutral constitution, Qi-deficiency constitution, Yang-deficiency constitution, Yin-deficiency constitution, Phlegm-damp constitution, Damp-heat constitution, Blood-stagnation constitution, Qi-stagnation constitution, and Special diathesis constitution. For each item, subjects selected 1 from 5 answers (not at all, few, sometimes, often, always), and given a respective score (1–5). For each subscale, the original score was first calculated by summing of the scores for each item. The derived score of each subscale was calculated from the following formula: (original score−the possible lowest score of the subscale)/(possible highest score-possible lowest score) × 100, ranging from 0 to 100 points. Neutral constitution referred to the patients with derived scores of the 8 unbalanced constitutions being <40 points, and the derived score of the Neutral constitution being ≥60 points. If the score of any constitution subscale was ≥40 points, unbalanced constitutions were diagnosed. Patients with 2 or more constitutional types ≥40 points, subjects were diagnosed with constitution of the highest subscale score.^[97,98]^6.SQSSP will be used to evaluate subjective feelings of symptoms induced by spinal problems. It consists of 10 items that indicate 9 basic symptom factors induced by spinal problems: the relaxation or tensity or pain and fatigue of various parts of body, the degree of limitation in various parts of body, sense of suppression in the chest, palpitation, fatigue, emotional stability, insomnia, quality of life, and self-feeling in present.7.SQTSS will be adopted to make self-evaluation about Qigong training. It has 2 subscales which assess self-evaluation during training and self-evaluation after training. The Self-made Qigong Training Self-evaluation Scale, from the perspective of participants themselves, provides a lot of information about training quality and effects of Qigong training on physiology, respiratory function, and psychology.

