### Statistical analysis

2.16

Collected data will be recorded on standardized forms. Descriptive statistics will be calculated for dependent and independent variables. This analysis will include summary statistics of demographic information and outcome measures. Continuous variables will be summarized as mean (SD) ± standard deviation for normal distribution, and median (IQR) ± interquartile range for non-normal distribution. Normality will be tested using *Kolmogorov–Smirnov* test and categorical variables will be presented with frequencies or percentages. Appropriate transformations will be applied in cases of non-normal distribution. For the variables with a normal distribution, differences in terms of outcomes between groups will be compared using an independent *T-*test. If the variables have a non-normal distribution of ordinal level, statistical comparison between groups will be made by using the *Mann– Whitney U* test even after suitable transformations. Measures with a discrete distribution will be expressed as percentages and analyzed by the *X*^*2*^ or Fisher's exact test as appropriate. Subgroup analysis will be performed according to participants’ gender, personality, and constitution of TCM. Analysis of variance (ANOVA) will be used for the repeated measurement data, and *post-hoc* comparison between groups at different assessment time points will be conducted using multiple comparisons with adjustment to the type 1 error rate. Analysis of the primary and secondary outcomes will be on the basis of intention-to-treat (ITT) population and per-protocol (PP) population. The result of the ITT analysis will be compared with that of the PP analysis to check whether the results are consistent or not. If the statistical results of the ITT and PP population data are the same, the results will be deemed to be reliable; if they are contrary, we intend to adopt the results of the ITT population. The method of processing missing data will be the last observation carried forward (LOCF). This refers to assigning the last observed value of the end point indicator to the subsequent missing evaluation point; that is, the last observation response will be considered to be the study end point. Safety will be evaluated by tabulations of AEs, and will be presented with descriptive statistics for each group. A chi-square test or a Fisher's exact test will be used to compare the frequency difference in AEs between the 2 groups, and severe AEs will be listed in detail. To explore potential factors which might influence adherence, a logistic regression model and a linear mixed-effects model will be used and adjusted for potential confounders. Adherence-related data will be taken from training log records. All statistical tests will be implemented using IBM SPSS 21.0 with bilateral inspection. The level of statistical significance is assumed at 2-sided *P* value <.05.

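### Adverse events are likely to be picked up more intensively in the TCPSQ arm during the 10-week intervention, and the planned between-arm AE test makes no allowance for this

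*Protocol article*

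**What the plan says.** **The test.** Section 2.16 tabulates AEs by group and states that a chi-square or Fisher's exact test "will be used to compare the frequency difference in AEs between the 2 groups". The general rule on error applies: "The level of statistical significance is assumed at 2-sided" P below .05. Nothing is said about how the AEs entering the test must have been found.

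**Sources open to both arms.** Section 2.4 provides a log book: "A log book will be given to each participant to monitor involvement and practice" TCPSQ, "as well as any reporting of adverse events (AEs"). The abstract has blinded independent assessors evaluate adverse events and safety at baseline and at weeks 6, 11 and 19, with no restriction to one arm. Section 2.11.3 also requires a daily diary from both groups. Its listed content is activity, sedentary time and sleeping time, not symptoms.

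**Contact in the TCPSQ arm only.** Section 2.11.3 sets supervised training on 5 days a week for 10 weeks and adds: "The instructors will visit each individual to ensure that the movements are being correctly practiced". It also requires a training self-evaluation scale whose items include pain, fatigue, perspiration and "abnormal physical and mental reaction, level of coordination between body and mind during and after training". The number of completed scales per day counts towards compliance. That sentence speaks of all participants, but it stands in the training regimen, and the Discussion assigns the scale to the TCPSQ group. Section 2.14 names the coaches among those who deal with a participant's AE. Section 2.11.2 gives controls no training, and so no such contact.

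**The concern.** A two-group test of AE frequency reads as a comparison of harm only if an event of a given kind has about the same chance of being recorded in either arm. Here one arm is seen on most weekdays by staff with a role in AE handling and is prompted in writing about bodily and mental reactions. The other is not.

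The events most exposed are ordinary complaints that section 2.14 lists as examples, such as headache, muscle soreness and irritability. Students have these anyway and may or may not write them down.

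Safety is part of the primary aim (section 2.1). If the TCPSQ arm shows more AEs, the report cannot separate harm from closer observation. Equally, a real excess could be explained away as an artefact of observation.

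**Working it through.** The documents state no AE risk, no capture rate and no power for the safety comparison, so there is no figure of the plan to reproduce. The check has two parts.

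**1. Contact during the intervention, side by side**

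| Source | TCPSQ | Control |
|---|---|---|
| Log book (2.4) | yes | yes |
| Scheduled AE evaluation, weeks 6 and 11 (abstract) | yes | yes |
| Daily diary, no symptom item (2.11.3) | yes | yes |
| Supervised sessions (2.11.3) | 5 × 10 = 50 | 0 |
| Training scale with symptom prompts (2.11.3, Discussion) | yes | no |

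The common sources add equally to both arms. The last two rows come on top of them in one arm only.

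**2. What unequal capture does to the test**

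Inputs from the documents: 40 per arm (section 2.3: "Considering a 20% attrition rate, a total of 80 participants are necessary, with 40 participants in each group"), two-sided 0.05, and Fisher's exact or the chi-square test. Assumed: the same true risk π in both arms, capture of 90% in TCPSQ, and capture c in controls varied from 90% down to 40%.

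- Observed risk = π × capture. With π = 0.30, TCPSQ shows 0.30 × 0.90 = 27%.
- Controls show 0.30 × c: 24% at c = 80%, 21% at 70%, 15% at 50% and 12% at 40%.
- Apparent risk ratio = 0.90 / c: 1.13, 1.29, 1.80 and 2.25.

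The false-positive rate is the sum, over all pairs (x, y) with p < 0.05, of Bin(x; 40, 0.90π) × Bin(y; 40, cπ). It was computed by full enumeration, with the chi-square test uncorrected.

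| Control capture | Fisher, π = 20% | Fisher, π = 30% | Fisher, π = 40% | Chi-square, π = 30% |
|---|---|---|---|---|
| 90% (equal) | 2.8% | 2.9% | 2.8% | 4.9% |
| 80% | 3.1% | 3.6% | 3.9% | 6.1% |
| 70% | 4.4% | 6.1% | 7.7% | 9.6% |
| 50% | 11% | 19% | 28% | 26% |
| 40% | 17% | 31% | 45% | 40% |

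With 30 per arm, the minimum named in section 2.3, the pattern is the same at lower rates. For example, at π = 40% and c = 50% Fisher gives 20% instead of 28%.

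In expected counts, at π = 30% and c = 50%, the arms show 40 × 0.27 = 10.8 and 40 × 0.15 = 6.0 participants with an AE. A table of 11 versus 6 out of 40 gives a Fisher p of 0.27. A typical trial with that gap would therefore not be significant, although the point estimate would mislead.

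**The case against.** The strongest objection is that the documented AE sources carry no arm restriction: the log book, the scheduled evaluation by blinded assessors, and reports to the researchers recorded on case report forms. Instructor visits are described as a check on movements. The training scale is described as a measure of training and compliance. No sentence routes either into the AE record. The visit chart (Table 1) is not shown, and a journal article may leave the AE enquiry to the full protocol.

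This has force and rules out three stronger readings.

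- *Controls are only passively logged.* A reader might infer this because section 2.13 does not mention AEs. The abstract contradicts it.
- *The test measures surveillance rather than harm.* The documents do not show this. It would need a large capture gap, and the table shows little effect at 80% control capture.
- *The problem is the same under any AE definition.* It is not. Section 2.14 first defines an AE regardless of cause, then as a lesion caused by the intervention. Under the second definition untrained controls could hardly have a countable AE, and the definition would drive the result. That contradiction needs its own correction. A cause-neutral definition alone would still leave unequal ascertainment.

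What the objection does not remove is the difference in opportunity. The scale's items overlap with the AEs listed in section 2.14. Coaches are named in AE handling. Section 2.14 follows AEs from the moment they come to the investigator's attention, and records their details during the intervention period, when the gap is widest. That these contacts raise the recorded AE count is an inference, but a reasonable one.

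**Conclusion.** The concern holds in moderate form. Ascertainment is likely to be more intensive in the TCPSQ arm during the 10-week intervention, and the AE test in section 2.16 is open to detection bias against TCPSQ.

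The size cannot be derived from the documents. With an assumed true risk of 20% to 40% in both arms and 90% capture in TCPSQ, the false-positive rate of Fisher's test stays at about 3% to 8% while controls capture at least 70% of their events. It reaches 11% to 28% at 50% capture and 17% to 45% at 40%. The bias is small for a mild gap and serious only for a wide one, and the plan provides no means of telling which applies.

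The conclusion assumes that training contacts lead to some additional AE records. If the full protocol confines AE recording to sources applied identically in both arms, the point reduces to saying so in section 2.16.

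**What to change.** In sections 2.14 and 2.16:

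1. Add one identical, cause-neutral AE question to the daily diary that both arms already keep.
2. Ask about AEs in the same words in both arms at the common visits (weeks 6, 11 and 19). Section 2.14 places AE recording on case report forms in the intervention period, so its wording must be extended to cover week 19.
3. Base the chi-square or Fisher comparison on AEs from these common sources only.
4. List events known only from training sessions or the training self-evaluation scale in full, separately and descriptively, for the TCPSQ arm.

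Worsening on SCL-90 or on the spinal-symptom questionnaire (whose items include "sense of suppression in the chest, palpitation, fatigue, emotional stability, insomnia") may be shown as supporting information. It should not become the AE comparison: no threshold for worsening is given, it would add many comparisons, and both instruments are already outcomes.

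The cost is protocol wording, one diary question and one extra listing. The drawback is that the tested count omits some events seen only in sessions, which may include plausible harms of the training. The listing must therefore be reported beside the test, so that a null result is not read as evidence of safety on its own.

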
## Ethics issue

3

This study protocol is conducted in accordance with the Declaration of Helsinki.^[99]^ The study protocol and consent forms were approved by the ethics committee of BUCM (approval number: 2018BZHYLL0109), where the study will take place. The researcher will explain the benefits and risks of participation in the study to each participant and will provide an informed consent form approved by the Ethics Committee. All participants will be fully informed about the trial, and will sign the voluntary written informed consent form prior to participation before the baseline assessment. All participants will have the right to withdraw from the study at any time. The research ethics committee will also be in charge of supervising all procedures carried out in our study, including participants’ recruitment, randomization, conduct of the study and data storage. In cases of changes to our study protocol, we have to hand in a written application to the research ethics committee. The committee members will then decide whether it is necessary to change the study protocol.

## Dissemination

4

The study protocol has been registered, and is available on the Chinese Clinical Trial Register website (registered inChiCTR.org with the identifier ChiCTR-BON-17010840). This study will be published in scientific journals to target a wide range of groups if possible regardless of the magnitude or direction of effect. Study results will also be sent to study participants and disseminated to researchers, healthcare providers and healthcare professionals, as well as the general public through courses, presentations and internet regardless of the magnitude or direction of effect. No professional writers will be employed.

## Discussion

5

The health and well-being of college or university students group is important, not only due to their potential societal influence, but also because many lifestyle-related attitudes and habits are formed at this stage and persist across the life span.^[2,3,100]^ Time at university is enjoyable for most students, but students are also exposed to various psychosocial and physical hazards, sometimes with decreased connectedness to their families.^[101]^ Qigong is one of the essential elements of traditional Chinese culture. Qigong therapy, an important branch of TCM, has a history going back thousands of year.^[40–43]^ Which is the skill of body-mind exercise that integrates the 3 adjustments of body, breath and mind into “one.”^[40–45,75]^ Compared with conventional exercise modalities (e.g., resistance training, muscular endurance training, and strength training), Qigong is simple, soft and relax, and the playing space and exercise equipment are not restrictive.^[46,49,50,61,63,64]^ In recent years, an increasing number of studies have documented the effectiveness of Qigong exercise in helping people improve their physical health and reduce anxiety, improve hedonistic tone, have beneficial effects on the cardiovascular, respiratory and endocrine systems, and strengthen the immune system.^[41,42,46,51,56,64–75,102–106]^

*PSQ* is a traditional Qigong form practiced mainly in a standing posture. During its long history, *PSQ* has branched into various styles, most of which adopt the standing posture, and hence it is known as *PSQ.* The phrase “Stand alone and guard your spirit” in *Plain Questions—On Health-Keeping of Remote Antiquity or Su Wen—Shang Gu Tian Zhen Lun* implies *post standing*. Similar phrases, such as “leaning against the wall” and “upstanding posture,” are found in *General Treatise on Etiology and Symptomology of Various Diseases or Zhu Bing Yuan Hou Lun*. *PSQ* was popularized during the 1950s as one of the main Medical Qigong forms in China. In over 60 years of clinical application, it has proven its efficacy in treating many sorts of disease.^[75]^ As we know, *PSQ* is practiced mainly in a standing posture. During practice, the upper body and 4 limbs are kept in a fixed posture to train the static force of the muscles and to keep the mind focused. On the one hand, it helps relax the central nervous system and improve the self-controlling ability of the autonomic nervous system and coordination of the peripheral nervous system. The enhancement of the overall function of the nervous system contributes to the balance and harmony within the body. On the other hand, it promotes blood circulation, improves blood supply to the organs and tissues, and increases the amount of blood flowing back to the heart, strengthening the metabolism. Thus, this form has been recognized as an important practice for strengthening the body and improving the breath, mind.^[75–88]^

*TCPSQ* is one of common forms of *PSQ*. It is characterized by 3 circles: that between the hands, the arms, and the arches of the feet, in addition to the low, medium, and high postures based on the angle of knee flexion. In terms of breath and mind adjustment, it mainly employs normal abdominal breathing and gradually increases the intensity of concentration of the mind on the lower Dantian.^[75]^ The effect of this *PSQ* on the circulatory and respiratory systems is evident. It improves respiratory efficiency and increases blood and oxygen supply in the peripheral tissues by expanding the movement of the diaphragm and regulating myptasis of the lung. Moreover, it has a comprehensive effect on the motor system, coordinating the movements of the shoulder, elbow, wrist, hip, kenn, ankle, and toe joints, and promotes return of venous blood in the lower extremities. Hence it is often used to treat arthropathy, spinal disease, microcirculatory disorders due to diabetes, and arteriolar spasm due to hypertension As an aerobic exercise, previous studies have indicated that *TCPSQ* exercise program can improve sleep quality, psychological well-being for adults.^[75–77,80,83–88]^ But there is currently a lack of evidence regarding the associations between *TCPSQ* and physical fitness, as well as self-reported symptom intensity, anxiety, depression, self-esteem, and quality of sleep. In addition, from a Qigong point of view, the content of Qigong is based on the “the 3 adjustments” of body, breath, and mind. The aim of the 3 adjustments is to achieve a state of harmonious unity-integrating these adjustments into “one.”^[40,75]^ There is a popular belief that the 3 adjustments themselves stand for Qigong. But attention needs to be paid to the rest of the definition: the state of unity. This state of oneness is the criterion that distinguishes Qigong form ordinary physical exercises, in which the 3 adjustments are practiced independently, not unified. It is believe that it is easier to achieve this state of oneness from practicing *TCPSQ.*^[75]^ However, related research is not found. In this trial, we will apply modern devices including the *Nuamps 40 channel EEG signal recording and analysis system, Footscan Balance 7.7 acquisition and recording system, Spinal-mouse Spinal morphology measuring instrument* and *MP150 multiple-channel electrophysiological recording device* to synchronously measure the change of “the 3 adjustments” of body, breath, and mind and correlation analyses state of harmonious unity-integrating these adjustments into “one” in *TCPSQ state.* Moreover, it also further compares the difference between *Qigong state* and natural state. Furthermore, we will deeply explore the influence of *TCPSQ* on college students with different personality and constitution of TCM. This trial focuses on a college student population. Through a 10-week intervention with *TCPSQ*, results from a range of primary and secondary outcome measures will provide the clear information about difference in physical and psychological outcomes between *TCPSQ* and usual unaltered lifestyle control group. In this trial, we scrupulously performed the rigorous randomized, parallel-controlled, assessor-blinded and statistician-blinded design with an appropriate sample (n = 80) to evaluate the effectiveness and safety, feasibility of *TCPSQ* on the physical and mental health of college students. We will arrange 2 qualified teachers to serve as the coaches in order to ensure the standardized intervention training for participants. Participants in *TCPSQ* group will be gathered to do the exercise at a fixed setting and time and required to fill self-made *TCPSQ* training Self-evaluation Scale. To control the trial bias, all participants in both groups will be required to record their PA and sport diary as well as the sedentary time and sleeping time everyday throughout this study. Furthermore, the result evaluators and statistical analysts will be blinded to ensure the authenticity and objectivity of the trial results.

Initially, one of strengths of this study is that strict, complete, randomization, and adequate concealment will be used in our trial. What is more, the extensive physical and psychological outcomes assessment on several levels involving bioelectrical activity of cortical neurons, biomechanical balance of spinal column morphological balance of spinal column, degree of thoracic breathing and abdominal breathing, electrical activity of the heart, cardiopulmonary function assessment will make it possible to explore the mechanism of action of *TCPSQ* which offer a comprehensive understanding on the adjustment of body, breath, and mind, allowing the researchers to investigate the relationship between subjective scales and objective indicators. At the same time, using the SQTSS to appraise training quality and effects of Qigong training on physiology, respiratory function and psychology from the perspective of participants themselves is also the unique highlight of this study.

The undeniable fact is that several potential limitations may occur in this protocol. Ideally, everyone involved in an RCT should be blinded, but this is not always feasible in the nonpharmacological trials,^[107]^ therefore performance bias may be inevitable. Although the participants and exercise coaches are not blinded and the psychological outcome measures are participants’ self-reported, the development of some form of sham intervention for use in future studies of Qigong is a desirable goal, and we will make every effort to ensure that outcome assessors, laboratory technicians, data managers, and statisticians are unaware of the treatment allocations and train the whole research team, inform the participants about the details of self-report scales. Second, all participants will come from one and the same medical university, which may decrease the sample representativeness. Third, limitations of this pilot study are the relatively small sample size (only 80 participants) because the sample size calculation process is not applied in this study. Thus we will compare the effect size between groups in order to form larger-scale trials and add subjective-objective quantitative indicators in future research.

In summary, this is the first RCT protocol from the perspective of Qigong connotation to systematically evaluate the effect of *TCPSQ* for the physical and mental health of a college student population. If this study demonstrates a significant intervention effect, this would provide a preliminary higher-quality evidence and establish a further guidance for the application of *TCPSQ* exercise program among a college student population.
